##### Health Outcomes

Standard procedures in the pediatric obesity clinic will be used by trained nursing or medical professionals to measure resting heart rate and blood pressure of children. In addition, results from routine blood tests assessing glucose and hemoglobin A_1c_ levels will be obtained from the child’s medical records.

##### Dietary Intake

Children will complete a 24-hour dietary recall by using the Automated Self-administered 24-hour Recall (ASA24) system. ASA24 is a free, secure web-based tool developed by the National Cancer Institute for research use. The ASA24-2018 was developed for children and adults aged 10 years and older and guides participants through the completion of a 24-hour dietary recall by asking about food intake and estimated portion sizes during the previous day. Responses are scored using the US Department of Agriculture’s Food and Nutrient Database for Dietary Studies.

##### Physical Activity

Children will wear an ActiGraph GT3X+ Activity Monitor on their waist for 24 hours a day for 1 week. The ActiGraph GT3X + Activity Monitor [22] measures child energy expenditure. After wearing the device for 7 days, families will return the actigraph via a self-addressed stamped envelope provided by research personnel at each assessment time point.

##### Self-Efficacy

To assess self-efficacy for eating healthier and engaging in physical activity, children will complete the Child Dietary Self-Efficacy Scale [23], which consists of 15 items that children answer using a 3-point Likert scale. Children will also complete the Self-Efficacy for Physical Activity Scale [24], which consists of 5 items specifically regarding the management of physical activity–related barriers. Both measures have been used previously in pediatric research and have acceptable reliability and validity.

##### Health-Related Quality of Life

To assess child quality of life, the Pediatric Quality of Life Inventory (PedsQL) [25] will be utilized. The PedsQL consists of 23 items and has been utilized with a variety of pediatric populations, including obesity, and it has good reliability and validity.

##### Treatment Satisfaction

Upon posttreatment assessment, children will complete the treatment satisfaction questionnaire, which was developed for this study and based on a previous study [26]. The questionnaire asks children to rate how much they agree or disagree with 10 statements.

#### Parent-Completed Questionnaires and Assessments

##### Demographic and Health History Information

At the baseline assessment, parents will complete a demographic questionnaire to obtain information about the child and parent. In addition, parents will answer questions about their child’s and their own medical history. Parents will also be asked to provide their contact information, specifically postal address, phone numbers, and email addresses and the name and phone number of another family member the research team can contact if we are unable to contact the parent.

##### Height and Weight

Parent height and weight will be measured using the same aforementioned methods used for children. Measurements will be used to calculate parent BMI and determine parent weight status.

##### Home-Food Environment

The Home Food Inventory [27] will be completed by parents to assess the availability of healthy and unhealthy food at home. The measure was developed for use in health promotion research and has demonstrated adequate reliability and validity.

##### Child Health-Related Quality of Life

Parents will complete the parent-proxy form of the PedsQL [25] to provide perceptions of their children’s quality of life. The parent-proxy form of the PedsQL has demonstrated good reliability and validity.

##### Treatment Satisfaction

Parents will also complete the treatment satisfaction questionnaire developed for this study upon posttreatment assessment [26]. The questionnaire asks parents to rate how much they agree or disagree with 12 statements about the RPMS.

#### Compensation

Families will receive compensation for completing each assessment. Total compensation for participating in the study will be US $90 during the 6-month study period.

### Statistical Analyses

To examine aim 1, descriptive statistics (including mean [SD] and percentage values) of engagement with the RPMS will be used to examine feasibility and satisfaction scores on the basis of child and parent reports completed during the posttreatment assessment. To examine aim 2—initial effectiveness of the RPMS—repeated-measures analysis of variance will be conducted to determine whether there are significant differences in outcomes over time. Two-sample *t* tests will be used to compare differences in outcomes from pre- to posttreatment, pretreatment to follow-up, and posttreatment to follow-up. If necessary (eg, outcome data are skewed), nonparametric tests will be used to compare pretreatment, posttreatment, and follow-up scores. Maximum likelihood techniques will be utilized for missing data to provide unbiased and accurate estimates of variables regardless of the pattern of missing data (ie, random or completely random). Statistical significance will be set at *P*<.05.

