**Methods:**

Participants will include 45 youth with obesity and their parents. Families will receive standard care in the clinic and the RPMS for 3 months. The RPMS consists of a tablet, weight scale, and pedometer. The system provides daily educational content and involves the use of the pedometer and weekly weigh-ins. Children and parents will complete baseline, posttreatment (month 3), and follow-up assessments (month 6). The primary aim of the study is to examine feasibility and satisfaction with the RPMS and assess its initial effectiveness.

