**Results:**

We hypothesize high feasibility and satisfaction, with rates over 75%. Furthermore, after RPMS treatment, children will exhibit improved weight status, health outcomes, dietary intake, physical activity, health-related quality of life, self-efficacy, and home-food environment compared to before treatment. These gains are expected to persist at follow-up.

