### Study Aims

The primary objective of this open trial is to pilot test an RPMS designed to provide supplemental health care to youth who are receiving specialty medical care in a multidisciplinary pediatric obesity clinic. Specifically, we will assess initial feasibility and satisfaction and examine initial effectiveness of the RPMS for 3 months. We hypothesize high feasibility with the use of the RPMS and satisfaction rates over 75%, and after treatment children are expected to exhibit improved health outcomes compared to before treatment and their parents are expected to report improvements in their children’s health-related quality of life and home-food environment.

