## Results

The study received ethics approval from the institutional review board in January 2019. Recruitment and enrollment began in August 2019. As of April 2021, 42 youth and their caregivers were enrolled in the study; however, participants continue to receive the RPMS intervention, and posttreatment and follow-up assessments are underway. Future outcomes will be published in professional peer-reviewed health-related research journals and presented at national, regional, or state-level professional meetings and conferences. Preliminary findings will be used to inform the development of a future study that will include a randomized controlled trial containing a larger sample of families and a standard care control group, evaluation of a refined RPMS, and cost-effectiveness analyses.

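### Satisfaction is measured only in families who complete the month-3 assessment, so the over-75% satisfaction hypothesis can look met among retained families without being met among all enrolled

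*Protocol article*

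**What the plan says.** The planned size is given in the Abstract (Methods): "Participants will include 45 youth with obesity and their parents". The Results section reports progress: "As of April 2021, 42 youth and their caregivers were enrolled in the study".

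The 75% figure appears twice. The Abstract (Results) says "We hypothesize high feasibility and satisfaction, with rates over 75" per cent. Study Aims says "We hypothesize high feasibility with the use of the RPMS and satisfaction rates over 75" per cent. The first attaches the figure to feasibility and satisfaction together. The second most naturally attaches it to satisfaction, though it can be read as covering both.

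Statistical Analyses makes aim 1 descriptive and gives the two components different sources. For feasibility, "descriptive statistics (including mean [SD] and percentage values) of engagement with the RPMS will be used to examine feasibility". For satisfaction, the source is "satisfaction scores on the basis of child and parent reports completed during the posttreatment assessment".

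The two Treatment Satisfaction subsections place the questionnaire at the posttreatment assessment only. For the child form, "The questionnaire asks children to rate how much they agree or disagree with 10 statements". For the parent form, "The questionnaire asks parents to rate how much they agree or disagree with 12 statements about the RPMS". Study Design places the posttreatment assessment at a routine clinic follow-up appointment after 3 months of use.

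**The concern.** A satisfaction rate built only from month-3 reports describes the families who stayed and answered. If families who leave are less satisfied than those who stay, the rate overstates satisfaction in the enrolled group. The article does not show that leavers are less satisfied, but the possibility is plausible, and the plan as written cannot detect it. The Introduction itself notes that consistent care is hard to maintain in underserved families, and the Discussion describes this clinic's population in those terms.

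The maximum-likelihood sentence in Statistical Analyses does not close the gap. It follows the aim 2 tests, and the missingness it names is random or completely random. A form left unanswered because the family was dissatisfied is neither.

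The sample is also small, so an observed rate just above 75% says little about where the true rate lies. This matters because the Discussion makes the pursuit of funding for a randomised study depend on whether the feasibility, satisfaction and effectiveness data look promising.

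**Working it through.** The article gives no derivation of the sample size or of the 75% figure, so there is no planned figure to reproduce.

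**Inputs from the article:** 45 families planned (Abstract, Participants); 42 enrolled by April 2021 (Results); threshold above 75% (Abstract, Study Aims).

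**Assumptions:** satisfaction is a yes/no per family for one type of respondent, because the article gives no rule turning the 10-item or 12-item form into a rate. Responder numbers of 45, 36 and 30 are illustrative (0%, 20% and 33% loss), because no dropout rate is given.

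**Step 1. Smallest count above 75%.** This is the smallest whole number x with x/n > 0.75. For n = 45, 0.75 × 45 = 33.75, so x = 34. For n = 36, 0.75 × 36 = 27 exactly, so x = 28. For n = 30, 0.75 × 30 = 22.5, so x = 23.

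**Step 2. Exact 95% interval.** The Clopper-Pearson limits are the 2.5% quantile of Beta(x, n − x + 1) and the 97.5% quantile of Beta(x + 1, n − x).

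**Step 3. Bounds over all 45 enrolled.** The lower bound is x/45 (no non-responder satisfied). The upper bound is (x + 45 − n)/45 (every non-responder satisfied).

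| Responders | Smallest count above 75% | Rate | Exact 95% CI | Bounds over 45 enrolled |
|---|---|---|---|---|
| 45 | 34 | 75.6% | 60.5% to 87.1% | 75.6% |
| 36 | 28 | 77.8% | 60.8% to 89.9% | 28/45 = 62.2% to 37/45 = 82.2% |
| 30 | 23 | 76.7% | 57.7% to 90.1% | 23/45 = 51.1% to 38/45 = 84.4% |

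With the 42 enrolled by April 2021 and full response, the smallest such count is 32/42 = 76.2%, with an interval of 60.5% to 87.9%.

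**Step 4. Break-even among non-responders.** Exceeding 75% of all 45 needs 34 satisfied families. With 28 of 36 responders satisfied, 34 − 28 = 6 of the 9 non-responders (67%) must also be satisfied. With 23 of 30, it is 34 − 23 = 11 of 15 (73%). Below those shares, the rate exceeds 75% among responders but not among all enrolled.

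**Step 5. Chance of an observed rate above 75% when the true rate is lower.** With full response this is P(X ≥ 34), X ~ Binomial(45, p): 2.2% at p = 0.60, 9.0% at 0.65, 26.2% at 0.70 and 54.6% at 0.75. Sampling error alone misleads with substantial probability only when the true rate is close to 75%.

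**The case against.** Several points on the other side stand.

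- **Feasibility.** A reader might infer that the whole over-75% claim rests on month-3 attenders. It does not. Feasibility rests on engagement with the system during the 3 months, and nothing limits that to attenders, so abandonment can show there.
- **No pass rule.** A reader might infer that the primary aim can be passed through attrition or chance. The 75% is a hypothesis in a descriptive pilot, the primary aim also covers initial effectiveness, and the Discussion speaks of promising data rather than of crossing a threshold.
- **Contradiction.** The two statements of the hypothesis differ, but Study Aims is ambiguous rather than in flat conflict with the Abstract.
- **Mean scores against a rate.** The analysis section lists percentages beside means, so a comparison with 75% is possible. The scoring rule, the denominator and the interval are details an article may leave to a fuller document, and their absence alone is no finding.
- **Stopping use is not the same as missing the visit.** The assessment falls at a routine clinic appointment, so a family that put the tablet away may still attend and report dissatisfaction. Payment for each assessment and a backup family contact also help retention.

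One might go further and require the lower 95% limit to exceed 75%. With 45 responders that needs 40/45 (88.9%), which would be met 31% of the time at a true rate of 85% and 9% at 80%. That is too strict for a pilot of this kind. Counting every non-responder as dissatisfied in the main analysis would also merge attendance with satisfaction.

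None of this changes the fact that the article itself fixes the source of the satisfaction data. Families with no month-3 report are outside it.

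**Conclusion.** The concern holds for satisfaction. The stated source leaves out families who drop out before the month-3 assessment, so an observed rate above 75% among responders could sit beside a rate below 75% among all enrolled. Under the assumed 20% and 33% losses, a rate that just clears 75% guarantees only 62.2% and 51.1% of the 45 enrolled. Those are lower bounds that apply if no non-responder was satisfied, not estimates of the bias. The direction of any bias depends on whether leavers are less satisfied, which the article neither shows nor lets the analysis examine.

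Separately, even with every family responding, 34/45 is compatible with a true rate from about 60% to 87%, so exceeding 75% should be presented as an estimate and not as demonstrated. The difference in wording between the Abstract and Study Aims is a smaller matter, but it leaves unclear whether feasibility carries a numerical benchmark.

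**What to change.** 1. Offer the existing satisfaction questionnaire by tablet, phone or mail to families who stop using the RPMS or miss the month-3 visit.
2. Report the satisfaction rate among responders separately for children and parents, each with the number responding out of all enrolled and an exact 95% interval.
3. Add a sensitivity bound that counts non-responders as not satisfied, labelled as a bound.
4. Describe the comparison with 75% as an estimate with its interval.
5. Word the 75% hypothesis identically in the Abstract and in Study Aims, stating whether it covers feasibility.

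The cost is some extra contact effort, mixed modes of completion (which should be recorded and reported), and possibly a less favourable published rate. Posttreatment assessments were still under way when the article was written, so on that timeline the remote option could still be used for families not yet assessed.

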### Study Design

This study will utilize an open trial design to examine the initial feasibility and effectiveness of implementing an RPMS in a pediatric obesity clinic. Participating families will receive standard care and the RPMS. After providing consent and assent, children and parents will complete questionnaires and objective measures as part of the pretreatment assessment. After using the RPMS for 3 months, families will complete the posttreatment assessment during a regularly scheduled follow-up appointment with health care providers at the pediatric weight management clinic. After an additional 3 months, participating families will also complete a follow-up assessment, similar to the pre- and posttreatment assessments, during a regularly scheduled clinic visit.

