### Participants

The study will recruit 45 families with a child aged 8-17 years who attends an outpatient pediatric obesity clinic and has a weight status in the obese range (BMI equal to or above the 95th percentile for age and gender), and parents and children who are fluent in English. Exclusion criteria are the following: (1) the child or parent having a history of cognitive impairment (developmental delay or intellectual disability) reported by the parent, which would impact their ability to understand and complete questionnaires or interact with the RPMS; and (2) the child having a medical condition, reported by parents, which may prohibit wearing of the actigraph device (eg, pacemaker).

Potentially eligible participants will be recruited through the pediatric weight management outpatient multidisciplinary clinic. When families present for a scheduled appointment, providers will provide them information about the study and ask if they are interested in knowing more about it. A trained research team member will discuss the study in more detail and obtain child assent, parent permission, and parent consent to participate. The research assistant will then assist the child and parent with the completion of baseline questionnaires and assessments.

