### Data Collection and Measures

Children and parents will complete the following measures and assessments at pretreatment (baseline), posttreatment (month 3), and follow-up (month 6) unless otherwise specified.

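### The pairwise time contrasts are assigned two-sample t tests although the same children and parents are measured at all three visits; read literally, this inflates each contrast's standard error

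*Protocol article*

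**What the plan says.** The design is a single-arm open trial. Under Study Design: "Participating families will receive standard care and the RPMS". The only control group mentioned belongs to a later study, described under Results as a "randomized controlled trial containing a larger sample of families and a standard care control group".

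The same participants are measured repeatedly, as the section on Data Collection and Measures sets out: "Children and parents will complete the following measures and assessments at pretreatment (baseline), posttreatment (month 3), and follow-up (month 6) unless otherwise specified". The hypothesis under Study Aims is one of change within participants: "after treatment children are expected to exhibit improved health outcomes compared to before treatment". The planned size, under Participants, is 45 families.

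For aim 2, the Statistical Analyses section first says that "repeated-measures analysis of variance will be conducted to determine whether there are significant differences in outcomes over time". The next sentence names the follow-up test: "Two-sample *t* tests will be used to compare differences in outcomes from pre- to posttreatment, pretreatment to follow-up, and posttreatment to follow-up". The section then allows unnamed nonparametric tests for skewed outcomes, plans maximum likelihood techniques for missing data, and sets significance at P<.05. The article nowhere describes the comparisons as paired, matched or dependent.

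**The concern.** A two-sample t test assumes that the two sets of values come from different, independent people. No contrast in this design meets that assumption, because each compares a set of children (or parents) with themselves at another visit. Stable differences between children, which cancel when each child's change is taken, go back into the error term. The ANOVA in the preceding sentence removes those differences, so the overall test and its own follow-up contrasts rest on different error models. A significant ANOVA could be followed by three non-significant contrasts for that reason alone.

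The contrasts matter because they address the before/after hypothesis and the expectation in the Abstract that gains persist to month 6. An oversized standard error can hide a real improvement. It can also hide a real relapse between month 3 and month 6, and the non-significant result might then be read as maintenance. The findings are meant to inform a randomized trial, so missed changes and overly wide intervals would carry into its planning.

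**Working it through.** The article gives no power calculation, SD, effect size or within-child correlation, so there is no figure of its own to reproduce. The check compares the two tests under stated assumptions.

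**Inputs**
- n = 45 pairs (Participants), assuming every child has both visits.
- Significance level 0.05 (Statistical Analyses), taken as two-sided because sidedness is not stated.
- Equal SD at each visit, set to 1 (assumed).
- Within-child correlation r = 0.3, 0.5, 0.8, 0.9 (assumed range).
- True mean change 0.2 SD (assumed).

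**Standard errors**
- Two-sample: SD × sqrt(2/n) = sqrt(2/45) = 0.211, whatever r is.
- Paired, which is also the true standard error of the mean change: SD × sqrt(2(1-r)/n). At r=0.5 this is sqrt(1/45) = 0.149.
- Ratio: 1/sqrt(1-r). At r=0.5 this is 0.211/0.149 = 1.41.

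**Smallest observed mean change that reaches P<.05**
- Two-sample, 88 df: 1.987 × 0.211 = 0.419 SD at every r.
- Paired, 44 df: 2.015 × the paired standard error. At r=0.5 this is 2.015 × 0.149 = 0.300 SD; at r=0.9 it is 2.015 × 0.0667 = 0.134 SD.

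**Size and power**

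Paired power comes from the noncentral t with 44 df and noncentrality 0.2 × sqrt(45)/sqrt(2(1-r)). For the two-sample test the usual noncentral-t formula does not apply, because it assumes r=0, where it gives 15.5%. Its behaviour on correlated data was found by simulating bivariate normal pairs, and confirmed by averaging the rejection probability over the sampling distribution of the two variances.

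| r | SE ratio | Actual size of nominal 5% two-sample test | Two-sample power, 0.2 SD | Paired power, 0.2 SD |
|---|---|---|---|---|
| 0.3 | 1.20 | about 2% | 11% | 20% |
| 0.5 | 1.41 | 0.6% | 7.8% | 26% |
| 0.8 | 2.24 | below 0.01% | 1.7% | 55% |
| 0.9 | 3.16 | essentially 0 | 0.3% | 83.5% |

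Hand check at r=0.5, treating the SDs as known: the two-sample test rejects when the observed change exceeds 0.419. Under no change that is 0.419/0.149 = 2.81 standard errors, a two-sided probability of about 0.5%. Under a 0.2 SD change it is (0.419 - 0.2)/0.149 = 1.47 standard errors, a probability of about 7%. Estimating the SDs moves these to 0.6% and 7.8%.

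At r=0 the two tests agree, apart from a trivial loss of degrees of freedom. In simulation the paired test held its size at about 5% for every r tried.

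**The case against.** The strongest reply is that *two-sample* is loose wording for a paired comparison. The preceding sentence specifies a repeated-measures analysis, the contrasts run between visits, and there is no second group. A slip is at least as plausible as an intended independent-groups analysis, so a reader should not infer that the authors mean to ignore the pairing or that the P values will certainly be wrong. What stands is that the sentence names a specific test, nothing else in the article restores the pairing, and an analyst who follows it would run the wrong one. This is a stated rule, not detail left to a fuller plan.

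Two stronger readings are tempting and not supported. One is that aim 2 as a whole loses most of its power. The repeated-measures ANOVA respects the within-child structure and is unaffected; only the three pairwise contrasts suffer. The other is that the error could produce false claims of benefit. With positive correlation the test rejects too rarely, not too often. Only a negative correlation would reverse this (size about 7.4% at r=-0.2), and that is unlikely for repeated measures on one child.

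It is also fair to say that outcomes will differ. A BMI z score should track closely within a child, while a single 24-hour dietary recall may not, and at r=0.3 the inflation is only 1.2. Finally, this is a pilot whose feasibility and satisfaction aim is descriptive. That limits the consequences but does not make the named test suitable.

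**Conclusion.** Wrong as written. The test named for all three time contrasts does not fit a single group measured repeatedly, and it contradicts the ANOVA beside it. If applied literally, each contrast's standard error is too large by 1/sqrt(1-r), from 1.2 times at r=0.3 to 3.2 times at r=0.9. Power for a modest change falls well below that of the paired test, and the gap widens as r rises. The mismatch between test and design is certain from the text. The size of the effect depends on assumptions that the article does not supply: positive r, equal SDs, 45 complete pairs and a 0.2 SD change. The harm is lost sensitivity and overly wide intervals in the pairwise contrasts only.

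**What to change.** In the Statistical Analyses section, replace *two-sample t tests* with *paired t tests on within-participant differences*. Where a rank test is needed for a pairwise contrast, name the Wilcoxon signed-rank test so that the fallback keeps the pairing too.

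An optional alternative is to take the three visit contrasts, with 95% confidence intervals, from one linear mixed model with visit as a categorical within-participant factor. This would also fit the maximum likelihood handling of missing data already planned, but the paired t test is enough to cure the defect.

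The cost is a change of phrase, with no new data and no change to the visits. The Results section reports assessments still underway in April 2021, so on the article's own account the correction could be made before analysis.

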## Introduction

Pediatric obesity is a critical public health issue in the United States. Serious comorbid health conditions including type 2 diabetes, heart disease, stroke, and cancers are common [1]. Younger individuals with obesity burden the health care system [2]. Specifically, pediatric obesity accounts for health care costs of over US $14 billion annually in the United States [3]. Efficacious pediatric obesity interventions are necessary to mitigate long-term health consequences and reduce health costs.

Standard care in multidisciplinary pediatric obesity clinics decrease adiposity in approximately 50% of treated youth [4,5]. However, providing and maintaining consistent care can be challenging when working with underserved children and families [6,7]. In Mississippi, over 50% of the state is rural, more than 35% of the population is Black or African American, and almost one-third of children live in poverty [8]. Mississippi also has the highest rates of pediatric obesity in the United States [9]. There is a significant need for innovative evidence-based technology to improve health and weight status.

Telemedicine use has increased owing to high rates of computer ownership, tablets, and cellphones, as well as easier internet access [10]. Insurance companies and health care organizations use telemedicine to support chronic disease management by developing remote patient monitoring systems (RPMSs) [10]. RPMSs provide patients with hardware and software that medically monitor health outcomes, provide educational information, automatically analyze health data, and alert patients and care providers of concerns [10]. RPMS efficacy studies have demonstrated improved health status in adults with chronic health conditions [11], such as diabetes [12], congestive heart failure [13], and obesity [14]. Nonetheless, applications of RPMSs in pediatric populations are limited. Four published studies have examined the applications of RPMSs in youth, having particularly focused on those with sleep apnea [15], cardiovascular implants [16], cancer [17], and type 1 diabetes [18]. These studies demonstrated feasibility, effectiveness, and reduced health care costs in pediatric populations; however, RPMSs have not been integrated into pediatric obesity clinics.

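### Maximum-likelihood handling of missing data is promised, but the analyses named for aim 2 do not carry it out, and data missing not at random are left out of account

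*Protocol article*

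**What the plan says.** All of the relevant text is in the Statistical Analyses section of the Protocol article. For aim 2 it fixes three kinds of analysis:

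- the main test: "repeated-measures analysis of variance will be conducted to determine whether there are significant differences in outcomes over time"
- the pairwise comparisons: "Two-sample *t* tests will be used to compare differences in outcomes from pre- to posttreatment, pretreatment to follow-up, and posttreatment to follow-up"
- the fallback: "If necessary (eg, outcome data are skewed), nonparametric tests will be used to compare pretreatment, posttreatment, and follow-up scores"

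It then turns to missing data: "Maximum likelihood techniques will be utilized for missing data to provide unbiased and accurate estimates of variables regardless of the pattern of missing data". The closing words, with the gloss that follows them, read "regardless of the pattern of missing data (ie, random or completely random". The section names no likelihood-based repeated-measures model and does not say how maximum likelihood connects to the three analyses. Data missing not at random are not mentioned.

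Two other places bear on the point. Study Design ties the month 3 and month 6 assessments to routine clinic appointments. The Introduction says of the population served that "providing and maintaining consistent care can be challenging when working with underserved children and families".

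**The concern.** The section attaches a property to analyses that do not have it. Classical repeated-measures ANOVA, and the rank tests for three related measurements, need a child's full set of visits. A t test uses only the values that were observed, and a rank test has no outcome likelihood to maximise. With complete data none of this matters. Once visits are missed, an analyst who follows the named tests does not obtain the estimates that the missing-data sentence promises, even under missing at random, which the article itself lists.

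The second part is the wording. The gloss treats random and completely random as if they were all the patterns there are. Dropout that depends on outcomes nobody observed is a third, and likelihood estimation does not remove the bias it causes. A family that leaves clinic care also loses its clinic-measured outcomes, so this case deserves acknowledgement. The study has one arm and compares before with after, so any selection in who returns enters the estimated change directly.

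**Working it through.** **Inputs from the article.** 45 children in a single arm; assessments at baseline, month 3 and month 6; the three named analyses; significance at P<.05. The article gives no dropout rate, SD, effect size or power figure, so there is no stated number to reproduce.

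**Inputs assumed for illustration.** SD 1 at each visit; the same correlation r between any two visits, 0.6 or 0.9; true change from baseline -0.20 SD at month 3 and month 6 (negative means improvement); dropout of about 20% or 35%; 1000 runs per setting. Where dropout depends on a variable, the log-odds slope is 1.5 per SD, an odds ratio of e^1.5 = 4.48. This is a strong dependence. Children with higher (worse) values are the ones lost.

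**Estimators of the baseline-to-month-6 change.** (a) Complete cases, as in classical repeated-measures ANOVA or a paired t test. (b) Difference of available means, as in a two-sample t test. (c) Multivariate-normal maximum likelihood. Rank tests were not simulated.

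**Results** (truth -0.20; ranges cover both correlations and both dropout rates; Monte Carlo standard error at most 0.006):

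| Dropout depends on | Complete cases | Available means | Maximum likelihood |
|---|---|---|---|
| nothing (completely random) | -0.20 to -0.21 | -0.19 to -0.21 | -0.20 to -0.21 |
| baseline (random) | -0.05 to -0.18 | -0.34 to -0.55 | -0.20 |
| month 3 value (random) | -0.20 | -0.34 to -0.54 | -0.20 to -0.21 |
| the unseen change (not at random) | -0.30 to -0.55 | -0.25 to -0.37 | -0.28 to -0.46 |

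**Check of the baseline row by hand.** Let s be the shift in the completers' baseline mean. Their month 6 mean then shifts by r·s, so:

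- available means: -0.20 + r·s
- complete cases: -0.20 + (r - 1)·s

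With r = 0.6 and 35% dropout, the available-means result of -0.436 gives s = (-0.436 + 0.20)/0.6 = -0.393. The complete-case value should then be -0.20 + 0.4 × 0.393 = -0.043; the simulation gave -0.050 (standard error 0.005). With r = 0.9, s = (-0.549 + 0.20)/0.9 = -0.388, predicting -0.20 + 0.1 × 0.388 = -0.161, against -0.163 simulated. The two agree.

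**Reading the table.** Under missing at random, the worst complete-case result loses (0.20 - 0.05)/0.20 = 75% of the true change. The worst available-means result overstates it by (0.55 - 0.20)/0.20 = 175%. The two errors go in opposite directions. Complete cases do well in the month 3 row because r was set equal for all visits, so selection on month 3 shifts baseline and month 6 by the same amount. That is a feature of the set-up, not a general protection. In the last row maximum likelihood overstates improvement by 0.281/0.20 - 1 = about 40% up to 0.457/0.20 - 1 = about 130%.

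**Numbers of children.** If the ANOVA were run in classical form, 20% dropout would leave 45 × 0.80 = 36 children and 35% would leave 45 × 0.65, about 29.

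**The case against.** The case for the plan is substantial, and much of it stands.

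- **The maximum-likelihood sentence is nearly right.** A reader who stops before the parenthesis might infer that the article claims unbiasedness under every mechanism. With the parenthesis the claim covers missing at random and completely at random, where maximum likelihood is valid under a correct model; the simulation agrees. What remains is loose wording and an unmentioned third case.
- **Outcome-related dropout is not in itself fatal.** Dropout driven by observed baseline or month 3 values is missing at random, and maximum likelihood handles it. Only dropout related to unobserved outcomes breaks it.
- **The plan does not say it will use complete cases.** A reader might infer that it falls back to them. The text says maximum likelihood will be used; a repeated-measures analysis can be fitted by likelihood, or likelihood estimates might feed the comparisons. Such detail may sit in a fuller document. What stands against the article is that it names specific tests alongside a property those tests lack and supplies no link. Nor would that reading rescue the rank tests.
- **Bias towards benefit is not documented.** Nothing says that families whose child is not improving miss visits, and in the baseline row complete cases understate benefit. The article also plans payment for completing each assessment and records an alternative family contact. These may reduce missing data, but they do not settle how it is analysed.
- **Inflated false positives cannot be charged to the choice of ANOVA.** Suppose the true change is zero, 30% drop out, and the odds of dropout rise 1.65-fold to 2.7-fold per SD of unfavourable change. A completers' t test then shows a spurious 0.14 to 0.25 SD improvement, and P<.05 in favour of benefit occurs in about 13% to 33% of trials instead of 2.5%. That illustrates an assumed missing-not-at-random mechanism, which a mixed model alone would not cure.

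**Conclusion.** The point holds in two limited parts. First, the analyses named for aim 2 do not, in their usual form, implement the likelihood handling promised, and under missing at random this can matter: against a true -0.20 SD, results ran from -0.05 to -0.55 where maximum likelihood gave -0.20 to -0.21. Second, the wording leaves no room for data missing not at random, which is plausible but undocumented in a single-arm study whose outcomes depend on clinic attendance; maximum likelihood then gave -0.28 to -0.46.

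All these sizes rest on assumed dropout rates, correlations and a strong assumed selection, and the direction would change with the mechanism. They show that the mismatch can matter, not what this trial's bias will be. The study is a pilot of initial effectiveness meant to inform a later randomized trial, and feasibility and satisfaction are summarised descriptively. The point should be corrected, but it does not undermine the study.

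**What to change.** 1. Make the aim 2 analysis a likelihood-based linear mixed model with visit as a categorical factor, using all available observations, and take the three pairwise contrasts from that model instead of from separate t tests. For skewed outcomes, a transformed scale within the same model would keep incomplete children in the analysis.
2. Replace the wording "regardless of the pattern of missing data (ie, random or completely random" with a statement that the estimates are valid under missing at random.
3. Add one missing-not-at-random sensitivity analysis, for example a delta shift towards worsening applied to missing month 3 and month 6 values. The mixed model does not replace this step.
4. Optionally, use the weekly home weights as auxiliary information for missing clinic weights. According to Remote Patient Monitoring they are collected only during the 3-month treatment period, so they can help for month 3 but not for month 6.

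The cost is a few reworded sentences and modest extra analysis. No new data or visits are needed.
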